## 9 Analysis of secondary outcome measures

The secondary outcome measures are presented in section 3.2.

Binary secondary outcome measures will be summarized as frequency with percentage for each arm. In the unadjusted analysis, they will be compared between the two treatment arms using Chi Square

test or Fisher's test. The adjusted analysis will involve a generalized mixed-effect regression model including the trial arms (fixed effect), the participating center (random effect) and unbalanced participant characteristics at baseline (fixed effects). Relative risk with 95% confidence intervals for treatment vs. control arms will be calculated in both unadjusted and adjusted analyses, with a confidence interval lower than 1 indicating superiority of the intervention over the control. The only continuous secondary outcome measures will be summarized as mean (SD) or median (IQR) for each arm. In the unadjusted analysis, it will be compared between the two treatment arms using Student's t-test or Mann-Whitney test. The adjusted analysis will involve a linear mixed-effect regression model including the trial arms (fixed effect), the participating center (random effect) and unbalanced participant characteristics at baseline (fixed effects). Mean difference with 95% confidence intervals for treatment vs. control arms will be calculated in both unadjusted and adjusted analyses, with a confidence interval excluding 0 indicating a difference of the intervention vs. the control.

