### **Secondary outcome measures**

2. Proportion of neonates with hypothermia (temperature <36.5°C) at NICU admission;
3. Proportion of neonates with moderate-severe hypothermia (temperature <36.0°C) at NICU admission;
4. Proportion of hyperthermic neonates (temperature >37.5°C) at NICU admission;
5. Temperature at 1 hour after NICU admission;
6. Proportion of intraventricular hemorrhage (all grades and grade III-IV);
7. Proportion of respiratory distress syndrome (RDS);
8. Proportion of late onset sepsis;
9. Proportion of bronchopulmonary dysplasia;
10. Mortality before hospital discharge.

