### 3.2 Endpoints

Primary:

- To compare the proportion of neonates in the normal thermal range (temperature 36.5-37.5°C) at NICU admission.

Secondary:

- To compare the proportion of neonates with hypothermia (temperature  $<36.5^{\circ}\text{C}$ ) at NICU admission;
- To compare the proportion of neonates with moderate-severe hypothermia (temperature  $<36.0^{\circ}\text{C}$ ) at NICU admission;
- To compare the proportion of hyperthermic neonates (temperature  $>37.5^{\circ}\text{C}$ ) at NICU admission;
- To compare the temperature at 1 hour after NICU admission;
- To compare the proportion of intraventricular hemorrhage (all grades and grade III-IV);
- To compare the proportion of respiratory distress syndrome (RDS);
- To compare the proportion of late onset sepsis;
- To compare the proportion of bronchopulmonary dysplasia;
- To compare the mortality before hospital discharge.

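### SAP section 9 reads a relative-risk interval below 1 as superiority of drying for bronchopulmonary dysplasia and late-onset sepsis, but the plan does not say how infants who die before diagnosis are counted

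*Combined protocol and SAP*

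**What the plan says.** The protocol's secondary outcomes include "Proportion of late onset sepsis", the proportion with BPD and, as a separate item, "Mortality before hospital discharge". SAP section 3.2 repeats them as three unconnected comparisons: "To compare the proportion of late onset sepsis", "To compare the proportion of bronchopulmonary dysplasia" and "To compare the mortality before hospital discharge".

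SAP section 9 treats all binary secondary outcomes alike. "Binary secondary outcome measures will be summarized as frequency with percentage for each arm", followed by a chi-square or Fisher's test and a mixed model with arm, centre and imbalanced baseline characteristics. The relative risk is then read by one rule, "with a confidence interval lower than 1 indicating superiority of the intervention over the control".

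The analysis is by intention to treat (SAP 6.2), and follow-up ends at death or discharge (SAP 4.1). Neither document gives an assessment time or a denominator for BPD or late-onset sepsis, a rule for an infant who dies before either could be diagnosed, a composite with death, or a competing-event method. The missing-data section (SAP 6.4) does not mention death.

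**The concern.** Both diagnoses require an infant to live long enough to receive them. If every randomised infant stays in the denominator, which is the natural reading of intention to treat, an infant who dies first is scored as free of the disease. An arm with more early deaths then has fewer recorded cases, and the rule in SAP 9 counts that in its favour. The distortion also runs the other way: if drying kept fragile infants alive, BPD could rise and look like harm.

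The point is relevant here because the protocol's background links hypothermia at birth to adverse neonatal outcomes, and its abstract names mortality. SAP section 10 also repeats the outcome comparisons in infants of 23+0 to 27+6 weeks, where truncation by death is likely to be greatest. At stake is the reading of two secondary outcomes.

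**Working it through.** **The plan's own figure.** For 40% vs 55%, 80% power and two-sided 0.05, with pooled variance and no continuity correction:

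n = [1.960·√(2·0.475·0.525) + 0.842·√(0.40·0.60 + 0.55·0.45)]² / 0.15² = 172.8, so 173 per arm and 346 in total.

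This agrees with SAP section 5. The point does not affect it; 173 per arm is used below.

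**Assumed inputs.** The documents give no rates for death, BPD or sepsis. I assume control mortality 10%, drying mortality 16%, BPD in 25% of survivors, no effect of drying on any infant's lungs, and all deaths before diagnosis. The extra 6 points of deaths fall either on average-risk infants (25% BPD risk) or on frail ones (60% risk).

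**Formulas.** With all randomised infants in the denominator:
- Control BPD = (1 − 0.10) × 0.25 = 22.5%.
- Drying BPD = 22.5% − 6% × (BPD risk of the extra deaths).
- Death or BPD = mortality + BPD.
- SE(log RR) = √[(1−p₁)/(173p₁) + (1−p₀)/(173p₀)], where p₁ is drying and p₀ control.
- Chance of a false superiority reading = Φ(−1.96 − log RR/SE). This is 2.5% when RR = 1.

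| | Average-risk deaths | Frail deaths |
|---|---|---|
| BPD, drying vs control | 21.0% vs 22.5% | 18.9% vs 22.5% |
| RR, all randomised (95% CI expected at 173 per arm) | 0.93 (0.63–1.39) | 0.84 (0.55–1.27) |
| Chance that the whole CI is below 1 | about 5% | about 13% |
| RR, survivors only | 25%/25% = 1.00 | (18.9/84)/(22.5/90) = 0.90 |
| Death or BPD, drying vs control | 37.0% vs 32.5% | 34.9% vs 32.5% |
| RR, death or BPD | 1.14 | 1.07 |

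For frail deaths analysed in survivors only, the chance of a false superiority reading is about 7%.

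**Other assumed rates** (control mortality 10%, BPD in 20–40% of survivors, all randomised):
- Average-risk extra deaths: RR = (1 − drying mortality)/(1 − control mortality). The false-reading chance is 4–6% at drying mortality 15%, 7–12% at 20% and 11–22% at 25%.
- Extreme case, every extra death in an infant destined for BPD: 16–25% at drying mortality 15% and 51–76% at 20%. Death or BPD then has RR 1.00.
- Late-onset sepsis, 15–30% among infants at risk, deaths before the risk period 3% in control and 10% under drying: RR = 0.90/0.97 = 0.93, false-reading chance about 5–6%.

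**Reverse case.** With drying mortality 4% and the saved infants at 60% BPD risk, BPD is 22.5% + 3.6% = 26.1% (RR 1.16), while death or BPD is 30.1% vs 32.5% (RR 0.93).

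**Mortality as the safeguard.** Power to detect 10% vs 16% with 173 per arm is about 37–38%, depending on the approximation. It is 29% for 10% vs 15% and 74% for 10% vs 20%.

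**The case against.** The strongest reply is that the effect is modest and partly guarded against.

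- **The rule needs the whole interval below 1.** A reader might infer that excess deaths would by themselves produce a superiority claim. The documents do not support that: both intervals in the table include 1, and the false reading stays uncommon unless the excess is large or concentrated in high-risk infants. The deaths pull the result towards superiority and usually do no more.
- **The denominator is not stated.** It is tempting to say that the comparison is biased whichever denominator is used. With survivors only and average-risk deaths, the RR is 1.00. Bias then needs selective deaths.
- **Not every death matters.** An infant diagnosed before dying still counts as an event.
- **Mortality is its own outcome.** Unexpected deaths are also compared as serious adverse events (SAP safety analyses), and the monitoring board reviews all deaths. So one cannot say that the plan hides a survival benefit or a survival harm. What could be misread is the BPD or sepsis result.
- **The composite is a weak detector of harm.** In the table's scenarios its power to show harm is about 7–14%, below that of mortality alone, and in the extreme case it is neutral.

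All of this stands, and it limits the size of the point and argues against replacing the listed outcomes. It does not remove the gap: no section says how death before diagnosis is counted, the superiority sentence applies without qualification, and the separate mortality comparison has low power for an excess of this size.

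**Conclusion.** The concern holds in a limited form. For BPD and late-onset sepsis, SAP 9 attaches a superiority reading to outcomes that death can prevent from being observed, and the plan has no rule for such deaths. With all randomised infants in the denominator, excess mortality under drying moves the relative risk below 1. With survivors only, this happens only if the extra deaths are selective.

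Under the assumed rates of 10% vs 16% mortality and BPD in 25% of survivors, the spurious BPD relative risk is 0.84–0.93 and the false superiority chance about 5–13% against 2.5%. Death or BPD points the other way at 1.07–1.14. These sizes rest wholly on assumed rates, and on all deaths preceding diagnosis. The documents give no reason to expect drying to raise mortality; the weakness is in the reading rule. The primary outcome, measured at NICU admission, and the sample size are unaffected.

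**What to change.** Keep the listed outcomes and make these changes:

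1. In SAP 3.2 and 9, add two composites with all randomised infants in the denominator: death before discharge or BPD, and death before discharge or late-onset sepsis.
2. State the assessment time and denominator for BPD and late-onset sepsis on their own, and show both beside mortality by arm.
3. Limit the sentence in SAP 9 that reads an interval below 1 as superiority to these composites and to outcomes not truncated by death.
4. Record the addition in SAP section 13, which at present reports no change from the protocol's statistical approach.

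No new data are needed, since all components are already collected. If the sponsor also wants the composites in the protocol's outcome list, that is a protocol change and goes to the ethics committees. The downside is small: the composites are less specific to lung disease or infection, and they do not replace the mortality comparison for detecting harm.

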### **Statistical analysis**

Analysis will be performed according to the “intention to treat” approach. In case of deviations from the protocol regarding the contamination between arms, a per-protocol analysis will be also performed and the conclusion will be drawn according to the results of both analyses. Continuous

data will be expressed as mean and standard deviation, or median and interquartile range. Outcome measures will be compared between the two arms using Chi-square test, Fisher's test, Student *t* test or Mann-Whitney test as appropriate (unadjusted analysis). Regression models (adjusted analysis) will be estimated to evaluate the effect of drying on the outcome measures, adjusting for participating centers and potential confounders (i.e. clinically relevant variables or unbalanced characteristics at baseline). Effect sizes will be reported as risk ratio or mean difference with 95% confidence intervals. A sub-analysis according to gestational age ( $23^{+0}$ - $27^{+6}$  and  $28^{+0}$ - $31^{+6}$  weeks) will be performed with exploratory purpose. A p-value less than 0.05 will be considered statistically significant. Statistical analysis will be performed using R 4.1 software (R Foundation for Statistical Computing, Vienna, Austria) (19).

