### 6.2 Approach for main analysis

Data analysis will be performed using the statistical software packages R. All tests will be two-sided and a p-value less than 0.05 will be considered statistically significant. Statistical analysis will include an unadjusted analysis followed by an adjusted analysis.

Analysis will be performed according to the "intention to treat" (ITT) approach. In case of deviations from the protocol regarding the contamination between arms, a per-protocol analysis will be also performed, and the conclusion will be drawn according to the results of both analyses.

Additional sub-group analyses will be considered with exploratory purpose.

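### SAP section 9 concludes superiority of drying from any of nine binary secondary comparisons on its own 95% interval, giving roughly a one-in-five chance of a false claim if drying does nothing

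*Combined protocol and SAP*

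**What the plan says.** SAP section 9 deals with all binary secondary outcomes together. On what is reported, it says: "Relative risk with 95% confidence intervals for treatment vs. control arms will be calculated in both unadjusted and adjusted analyses". It then adds a rule for reading each of those intervals: "with a confidence interval lower than 1 indicating superiority of the intervention over the control". SAP section 8 words the primary outcome in parallel, with the direction reversed because normothermia is the desirable result. The one continuous secondary outcome, temperature one hour after admission, has a different rule: an interval that excludes 0 is taken to show a difference.

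The general threshold in SAP section 6.2 is "All tests will be two-sided and a p-value less than 0.05 will be considered statistically significant". The protocol, under Statistical analysis, has the same level: "A p-value less than 0.05 will be considered statistically significant".

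SAP section 3.2 lists eight binary secondary items. One of them holds two comparisons: "To compare the proportion of intraventricular hemorrhage (all grades and grade III-IV". That makes nine. They range from admission temperature categories to "To compare the proportion of bronchopulmonary dysplasia" and "To compare the mortality before hospital discharge".

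The exploratory label is given only to sub-group analyses, specifically the gestational-age strata (SAP sections 6.2, 6.3 and 10; protocol, Statistical analysis). The sample size (SAP section 5; protocol, Sample size) is derived from the primary outcome alone.

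**The concern.** A plan that lists secondary outcomes with uncorrected 95% intervals is ordinary. This one goes further and attaches a conclusion to each interval. The word superiority is used for the secondary outcomes just as it is for the primary, and nothing ranks one above the other when the conclusion is drawn. A trial that misses its primary outcome could therefore report that drying is superior for bronchopulmonary dysplasia, sepsis, haemorrhage or death, and cite the SAP as authority.

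This matters because, as the protocol's Background and Discussion explain, current guidance is to wrap very preterm infants without drying, and the trial is meant to inform that practice. Caregivers and outcome assessors are also unmasked, which is a further reason for caution about an isolated secondary finding.

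**Working it through.** **Inputs from the documents.** Two-sided 0.05 for all tests (SAP 6.2); 95% intervals and the superiority rule (SAP 9); the outcome list (SAP 3.2); 40% vs 55%, 80% power and 173 per arm (SAP 5).

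**The plan's own figure.** Two proportions, pooled variance, no continuity correction, mean proportion 0.475:

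n = [1.96 × √(2 × 0.475 × 0.525) + 0.8416 × √(0.40 × 0.60 + 0.55 × 0.45)]² / 0.15² = (1.3842 + 0.5876)² / 0.0225 = 172.8, so 173 per arm and 346 in total.

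The stated size is reproduced. It concerns the primary outcome only. The documents give no error rate for the secondary outcomes as a set.

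**Count.** <36.5 °C, <36.0 °C, >37.5 °C, haemorrhage of any grade, haemorrhage grade III-IV, respiratory distress syndrome, late-onset sepsis, bronchopulmonary dysplasia, death: nine. The continuous outcome is left out because its rule is not one of superiority.

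**Error per comparison.** With no effect, a two-sided 95% interval lies wholly below 1 with nominal probability 2.5%.

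**At least one false superiority claim, no effect on any outcome, one analysis:**

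| Case | Calculation | Result |
|---|---|---|
| Nine, independent | 1 − 0.975^9 | 20.4% |
| Nine, any dependence (upper bound) | 9 × 0.025 | 22.5% |
| Eight (haemorrhage counted once), independent | 1 − 0.975^8 | 18.3% |
| Six clinical outcomes only, independent | 1 − 0.975^6 | 14.1% |

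**Allowing for overlap.** Independence cannot be exact: <36.0 °C lies within <36.5 °C, severe haemorrhage lies within any haemorrhage, and hypothermia and hyperthermia exclude each other. Simulations used 173 per arm, Wald intervals for the log relative risk, and these nested structures. All event rates below are assumptions, except that normothermia was held at the SAP's control rate of 40%.

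| Assumed rate (%) | Set A | Set B | Set C |
|---|---|---|---|
| <36.0 °C | 20 | 25 | 15 |
| <36.5 °C | 50 | 55 | 40 |
| >37.5 °C | 10 | 5 | 20 |
| Haemorrhage, any / III-IV | 20 / 8 | 30 / 10 | 15 / 5 |
| Respiratory distress syndrome | 80 | 90 | 70 |
| Late-onset sepsis | 15 | 20 | 10 |
| Bronchopulmonary dysplasia | 25 | 30 | 20 |
| Death | 10 | 12 | 8 |
| **Any false superiority claim** | **18.6** | **18.2** | **18.2** |

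The normothermia proportion is the remainder after the <36.5 °C and >37.5 °C rows: 40% in sets A, B and C (100 − 50 − 10, 100 − 55 − 5, 100 − 40 − 20). In these runs (40,000 draws each) the temperature, haemorrhage and other outcomes were otherwise independent. The rates for single outcomes ran from 1.6% to 2.6%, mostly a little under 2.5%, which also pulls the total below 20.4%.

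With set A rates and a shared latent factor linking the outcomes (4,000 draws each), the results were 19.5%, 17.8%, 17.2% and 16.6% at assumed latent correlations of 0, 0.2, 0.4 and 0.6. The standard error is about √(0.18 × 0.82 / 4,000) = 0.6 percentage points, so the gap between 19.5% here and 18.6% in the larger run of the same case is within simulation noise.

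**The case against.** The strongest reply is that the clause only states direction. For the primary outcome more is better, so an interval above 1 favours drying; for the secondary outcomes fewer is better, so an interval below 1 does. There is one named primary outcome, the trial question and sample size rest on it, and no sentence lets a secondary result replace it. Many trials report secondary outcomes without correction.

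Much of this stands. There is nothing wrong with uncorrected intervals as estimates, and the primary outcome's own type I error is untouched by this point. But the direction-only reading does not remove the word superiority. The authors used an exploratory label elsewhere and did not use it here.

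Three of the nine comparisons are temperature categories closely tied to the primary outcome, so nine overstates the number of separate clinical claims. That is why the figure for the six clinical outcomes is given as well.

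A reader might also infer that the error grows because the rule is repeated in unadjusted, adjusted and per-protocol analyses. The documents do not support a figure for that. SAP section 9 does not say which of the unadjusted and covariate-adjusted intervals decides, or that either suffices. SAP section 6.2 says that, where there is contamination, the conclusion rests on the intention-to-treat and per-protocol results together; if the two must agree, false claims become fewer, not more.

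**Conclusion.** The point holds. Followed as written, SAP section 9 gives roughly a one-in-five chance of at least one false superiority conclusion for drying when drying has no effect: 20.4% if the nine comparisons are independent, about 17% to 19.5% in the simulations, and no more than 22.5% for one analysis whatever the dependence. For the six clinical outcomes alone it is 14.1% if independent. The first, third and fourth of these assume that each interval has its nominal 2.5% error on the side favouring drying; the simulated range rests on event rates and correlations that the documents do not give.

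Two stronger readings should be avoided. The independence value of 20% is not a ceiling; the bound is 22.5%. And the larger figure for a false difference in either direction, 1 − 0.95^9 = 37.0%, does not measure this rule, which concerns only intervals below 1.

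This should be corrected, because it changes what the trial may conclude. It does not put the primary analysis in doubt.

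**What to change.** 1. In SAP section 9, replace the superiority clause with: *Secondary outcomes are supportive; relative risks or mean differences with 95% CIs are reported and no conclusion of superiority is drawn from them.* Apply the same to the continuous outcome by removing the clause that reads an interval excluding 0 as a difference.
2. In SAP section 6.2 and in the protocol's Statistical analysis section, limit the conclusion of statistical significance to the primary outcome. If only section 9 were changed, the general 0.05 threshold would still apply to every secondary test. Changing both documents also keeps SAP section 13 true, which says the SAP departs in no way from the protocol's statistical approach.
3. If the sponsor wants a claim on a secondary outcome, it should pre-specify one outcome of its choice and test it only if the primary outcome is significant.

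The cost is a few sentences in two documents. No data item, model, estimate, interval or sample size changes. What is given up is the right to claim superiority on outcomes for which the trial was not sized.

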## 10. Exploratory Analyses

The outcome measures will be compared between the trial arms within strata of interest: participants with gestational age between 23+0 and 27+6 weeks, and participants with gestational age between 28 and 31+6 weeks). These analyses will be performed with exploratory purpose.

## 10 Safety Analyses

The trial protocol enlists unexpected death, severe hyperthermia (temperature >39°C) and hypothermia (temperature <35°C) as serious adverse events (SAEs). Occurrence of SAEs will be summarized as frequency with percentage and compared between arms using Chi Square test or Fisher's test.

## 11 Other Analyses

Additional analyses to be performed in the future will be discussed after the interim analysis and include in the SAP. Further analyses may subsequently be performed outside the scope of the SAP using the study data and published if appropriate, but they will be clearly described as post-hoc analyses.

## 13 Summary of Changes to the Protocol

The statistical analysis plan does not propose any changes to the statistical approach described in the referred protocol version (see front page).

